Within the 4 selected wards, all mapped households constitute the sampling frame, from which a systematic sample of households is drawn. Within each sampled household, all adults aged 18 years and older who meet the residency criterion are identified and invited to participate. Although the HDSS does not enroll every eligible adult resident because of resource constraints, this probability-based household sampling strategy, combined with formal power calculations, ensures that the resulting sample size is sufficient to address the primary study objectives. Using a baseline hypertension prevalence estimate of 30%, consistent with published data from Zimbabwe and comparable sub-Saharan African settings, a margin of error of ±2%, a 95% CI, and a design effect of 1.5 to account for household clustering, a minimum sample of approximately 3000 adults per site is required for robust prevalence estimation. This yields a total minimum analytical sample of 6000 adults across both rural and urban sites.

For the detection of a modest 2% absolute annual change in hypertension or diabetes prevalence (eg, from 30% to 32%) between surveillance rounds, with 80% statistical power and a 2-sided α of .05, a minimum of approximately 3500 participants per site per round is required. The estimated adult population across the 4 HDSS wards substantially exceeds this threshold, supporting the longitudinal objectives of the study. For rural-urban comparative analyses, equal allocation across the 2 sites provides 80% power to detect an absolute difference of 3% to 5% in key NCD outcomes. Subgroup analyses by sex, age group, and socioeconomic stratum are designated as exploratory, and appropriate corrections for multiple comparisons will be applied. Sample size calculations were performed in accordance with the WHO STEPwise approach to NCD risk factor surveillance (WHO STEPS) sample size guidance for population-based NCD surveys.

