### Follow-Up Procedures

Following the baseline census, longitudinal data collection rounds will be implemented annually over the 5-year surveillance period. Using the existing household and individual registers, field teams revisit each HHID and reverify the household roster, updating entries for births, deaths, in-migrations, out-migrations, and changes in marital status. Migration events are classified and dated using standard HDSS definitions, enabling calculation of person-time at risk and net migration rates. Migration events are identified and documented during each annual household roster update. New residents found in a previously mapped household who meet the standard residency criterion (at least 3 of the last 6 mo or intending to stay at least 6 mo) are classified as in-migrants, assigned a unique individual ID, and enrolled prospectively, with their origin and date of arrival recorded. Previously enrolled individuals confirmed by household members to have permanently departed the HDSS ward boundaries are classified as out-migrants, with their date of departure, destination, and reason for migration recorded and their follow-up record closed from that date, contributing person-time up to departure. Individuals who return after out-migration are reenrolled under their original ID, ensuring longitudinal continuity.

At each round, eligible adults are recontacted for updated interviews and measurements to estimate NCD prevalence and incidence, monitor changes in health-related behaviors and attitudes, and track risk factors over time. All recorded deaths are subjected to verbal autopsy using the WHO 2016 [31] standardized instrument administered on tablets; data are processed with automated cause-of-death assignment tools (eg, InterVA or InSilicoVA), given the limitations of vital registration in this setting.

Participant retention is managed through a structured recontact protocol whereby temporarily absent individuals receive at least 2 repeat visits at different times before being recorded as noncontactable for that round. At each round, the baseline characteristics of participants lost to follow-up will be compared with those retained to assess and account for potential attrition bias.

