### Data Management and Quality Assurance

A comprehensive data management framework underpins the HDSS. Data capture uses an electronic system built on REDCap with a longitudinal, relational database structure designed for population surveillance. Each household is assigned a unique HHID and each individual an INDID, enabling linkage of demographic episodes, survey data, and clinical measurements to calculate person-time at risk and event rates. Field tablets store encrypted records locally during the day; at the end of each field shift, data are synchronized via secure, password-protected connections to a central cloud-based server hosted on institutional infrastructure. Built-in validation rules (range checks, mandatory fields, and cross-variable consistency checks) run at the point of entry, with additional automated scripts on the server to detect duplicates, outliers, and missingness. Data collectors receive intensive training on the electronic tools, household listing procedures, eligibility screening, physical measurements, point-of-care devices, ethics, and field record keeping, and they are supervised by field coordinators who conduct random spot checks and reinterviews for quality control. All equipment is calibrated regularly according to manufacturer recommendations, and standard operating procedures govern every step from mapping and enrollment to follow-up and data cleaning.

To maintain secure linkage between participant identity and the assigned INDID, a separate access-restricted identity register mapping personal identifiers (full name, date of birth, and sex) to the INDID is maintained on an encrypted, password-protected server, accessible only to the principal investigator and senior data manager. All analytical datasets contain INDIDs only, with no direct personal identifiers, ensuring participant confidentiality. At each follow-up visit, fieldworkers verify the participant’s name, date of birth, and household ID verbally before accessing their longitudinal record, confirming correct identity linkage.

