### Data Analysis

The analytic plan encompasses descriptive statistics, robust prevalence and incidence estimations, and comparative analyses designed to quantify rural versus urban differences. Statistical software, primarily Stata (version 18; StataCorp LLC), will be employed. Numeric variables will be summarized using medians and IQRs, while categorical variables will be summarized using proportions. Logistic regression analyses (univariable and multivariable) will be used to identify and assess risk factors associated with NCDs, employing a hierarchical approach and stepwise backward elimination. The calculation of birth, mortality, prevalence, and incidence rates will be executed accordingly, and chi-square tests for trend will be used to analyze changes in NCD burden over time. Advanced statistical techniques, including regression and survival analyses, will facilitate robust estimation of NCD determinants and epidemiological transitions between the distinct study settings.

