## Results

The Zimbabwe HDSS was granted ethical approval by the Medical Research Council of Zimbabwe on July 30, 2024. Community profiling and household mapping were completed in both sites in the third quarter of 2024. Baseline data collection was completed in Mt Darwin (rural site) in December 2024 and in Bindura (urban site) in March 2025. Data cleaning and quality assurance procedures for the baseline dataset were initiated in April 2025, and statistical analysis of baseline prevalence, risk factor distributions, and rural-urban comparisons is projected for completion by the first quarter of 2026, with findings expected to be submitted for publication by the end of 2026. The first annual longitudinal follow-up round is planned for the second quarter of 2027, subject to funding availability. Subsequent follow-up rounds are scheduled annually through 2029, with longitudinal incidence estimates, demographic event rates, and NCD trend analyses expected to be published progressively from 2026 onward.

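### The only method assigned to change in NCD burden over time is a chi-square test for trend, with neither measure nor scores fixed, although the planned rounds are unequally spaced; regression on calendar time would suit the data and the annual-change target better

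*Protocol article*

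**What the plan says.** The Data Analysis section says of the measures: "The calculation of birth, mortality, prevalence, and incidence rates will be executed accordingly". The same sentence then says how change will be tested: "chi-square tests for trend will be used to analyze changes in NCD burden over time". It does not say which measure is tested, whether the test is for proportions or for person-time rates, or which scores the rounds receive. The next sentence says "Advanced statistical techniques, including regression and survival analyses, will facilitate robust estimation of NCD determinants" and extends this to transitions between the settings. Logistic regression is given to risk factors. None of these is assigned to the time trend.

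Person-time is planned elsewhere. Follow-Up Procedures dates migration events, "enabling calculation of person-time at risk and net migration rates". Data Management and Quality Assurance describes a database "enabling linkage of demographic episodes, survey data, and clinical measurements to calculate person-time at risk and event rates".

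On timing, Follow-Up Procedures says "longitudinal data collection rounds will be implemented annually over the 5-year surveillance period". Results gives baseline completion as December 2024 (rural) and March 2025 (urban), then: "The first annual longitudinal follow-up round is planned for the second quarter of 2027, subject to funding availability", with annual rounds to follow through 2029. Future Plans calls the rounds biannual. The only change over time that is sized is a "modest 2% absolute annual change in hypertension or diabetes prevalence" (Study Population and Sampling).

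**The concern.** The chi-square test for trend, as usually understood (Cochran-Armitage), compares binomial proportions across ordered groups. It has no place for unequal observation time. Here the first interval is more than twice as long as each later one, so at a constant rate it collects about twice as many new cases or deaths per person. The named test could read that excess as a downward trend.

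For prevalence the problem is milder. The test returns a p-value, whereas the plan's target is an annual change in percentage points. If rounds are scored 1, 2, 3, 4, the long first gap counts the same as the short ones.

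At stake is whether the trend results, which are meant to feed policy briefs, answer the annual-change question and are protected from an artefact of the calendar.

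**Working it through.** **The plan's own figures.** No figure is given for the trend test, so there is none to reproduce. The site sample used below does reproduce: 1.96² × 0.30 × 0.70 / 0.02² = 2,017, times the design effect 1.5 = 3,025, against about 3,000 stated.

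**Spacing.** December 2024 to April-June 2027 is 28 to 30 months. March 2025 to April-June 2027 is 25 to 27 months. Later rounds are annual, so 12 and 12 months. These run from the completion of baseline; adults measured earlier in that round wait longer.

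**Reading 1: proportion-based test on new cases per round.**
- Inputs: 70% of 3,000 free of hypertension gives 2,100 at risk. Numbers at risk are taken as 2,100, 1,890 and 1,785 (losses of 10% and 15%, assumed). Incidence is not in the article; 0.5, 2 and 4 per 100 person-years are assumptions.
- Interval risk at constant rate λ: p = 1 − exp(−λT).
- Statistic: z = Σ s(x − n·p̄) / √V, with s = 1, 2, 3 and V = p̄(1 − p̄)[Σns² − (Σns)²/N].
- Worked case, λ = 0.04, first interval 25 months: p = 8.0%, 3.9%, 3.9%; expected cases 167.9, 74.1, 70.0; p̄ = 312.0/5,775 = 0.0540; numerator −80.9; V = 197.7; z = −80.9/14.06 = −5.75.

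| Assumed rate per 100 person-years | First interval, 25 to 30 months | Each later interval | z |
|---|---|---|---|
| 0.5 | 1.0 to 1.2% | 0.5% | −2.1 to −2.7 |
| 2 | 4.1 to 4.9% | 2.0% | −4.1 to −5.4 |
| 4 | 8.0 to 9.5% | 3.9% | −5.8 to −7.5 |

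Calendar scores do not help here: the three follow-up rounds are a year apart, so their dates are a linear shift of 1, 2, 3 and z is unchanged. Only person-time removes the effect.

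A simulation under constant incidence (20,000 data sets per setting, 3,500 per site, 10% attrition per round assumed) agrees. At 2 per 100 person-years the proportion-based test rejects in 99 to 100% of data sets for hypertension. At 0.5 it rejects in 59 to 83% (hypertension) or 73 to 92% (diabetes, baseline 5.7%).

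**Reading 2: trend test on person-time rates.** In the same simulations rejection is 4.2 to 5.1%, that is, nominal.

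**Reading 3: trend test on round prevalence** (3,500 per round, rounds simulated as independent samples). With stable prevalence, downward rejection is 2.3 to 2.4%, the nominal tail. With a constant 3 per 100 person-years accumulating in a closed cohort, prevalence goes 30.0, 34.6, 36.5, 38.4% and downward rejection is 0.0%. Scoring matters little for the test: for a true rise of 0.5 points per year it rejects upward in 50% of data sets with round scores and 52% with calendar scores. It matters for any slope: regressing 0, 2.4, 3.4 and 4.4 years on round number gives 1.42 years per round, so a per-round slope would be about 1.4 times the annual one.

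**The case against.** The strongest objection is that Reading 1 is not in the article. A reader might infer that constant incidence will appear as a large, significant decline. The documents do not support that. They never say the test is run on new cases per round, they plan person-time rates in two sections, and a trend test for rates that uses person-time behaves correctly. The one change that is sized is in prevalence, where no false decline arises. Even under Reading 1 the size depends on an assumed incidence, and at the lowest rate a false finding is likely rather than certain. All of this stands.

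It is also fair that no trend slope is promised, so a per-round slope misread as annual is a hazard only if someone reports one.

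A last objection is that the variant and the scores are details for an analysis plan. That is right for the details, but the article goes further and names a method for change over time. In its usual form that method cannot use the planned person-time and does not estimate the annual change the study is sized on. Collecting person-time does not show that the named test uses it.

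**Conclusion.** The point holds in conditional form. The article assigns only a chi-square test for trend to change in burden, leaves measure and scores open, and gives dates that imply intervals of about 25 to 30, 12 and 12 months. Run on cases or deaths per round, the usual test would tend to turn a constant rate into an apparent decline (z from about −2 to −7.5 over assumed rates of 0.5 to 4 per 100 person-years, with assumed losses). Run on person-time rates, it would not. Run on prevalence, it is valid as a test of no change as far as spacing goes, but gives no annual estimate.

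The spacing rests on the Results dates, which depend on funding and sit beside conflicting descriptions of round frequency. This is a change that should be made because a better-suited method is available at almost no cost; it is not evidence that the planned results will be wrong.

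**What to change.** Replace the trend test with regression on calendar time:
- **Incidence and mortality:** Poisson regression with a log person-time offset, reporting a rate ratio per year with a confidence interval.
- **Prevalence:** a binomial model with years since baseline as the time variable and standard errors that allow for the same adults and households being re-measured, reporting percentage points per year with an interval.

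Do not attach a detectable slope computed as if rounds were independent samples. That calculation gives SE = √(0.21 × deff / (n × 10.67)) = 0.24 to 0.31 points per year, using 3,500 adults with design effect 1 and 3,000 with 1.5; times 2.80 this is about 0.7 to 0.9 points per year. It ignores within-person correlation, so any such figure should be recomputed with a stated correlation.

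Reconcile the annual rounds in Follow-Up Procedures, the biannual rounds in Future Plans and the dates in Results, so that the spacing is known.

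The cost is analysis wording only. The article already plans person-time and dated events, and the first follow-up is not due until 2027.

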### Study Aims

This paper describes the establishment of a Zimbabwe HDSS to address critical NCD surveillance gaps through 4 specific aims:

Establish a longitudinal, population-based HDSS spanning rural and urban sites to generate accurate, timely data on demographic dynamics, NCD burden, risk factors, and health care access through continuous household surveillance with regular follow-up.Characterize prevalence, incidence, and temporal trends of major NCDs—hypertension, diabetes, cardiovascular diseases, and chronic respiratory diseases—with particular emphasis on identifying undiagnosed and untreated cases through active case-finding and objective biomarker measurement.Quantify rural-urban differences in NCD burden, risk factor exposure profiles, health care–seeking behavior, treatment access, and health outcomes to inform geographically targeted interventions and evidence-based resource allocation.Generate actionable evidence informing national NCD policy development, strategic planning, resource allocation decisions, and intervention design through systematic integration with existing health systems and continuous stakeholder engagement.

By addressing fundamental gaps in existing surveillance infrastructure, this HDSS will provide the continuous, geographically granular, longitudinal data essential for evidence-based NCD prevention and control in Zimbabwe’s rapidly evolving epidemiological landscape.

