### Strengths and Limitations

The principal strengths of this rural-urban HDSS lie in its inherent methodological design, which provides longitudinal, context-rich insights into the dynamics of NCDs across contrasting environments. The systematic, repeated tracking of vital events, disease trends, and risk factors, employing harmonized, standardized methods in both rural and urban settings, facilitates robust comparisons of health transitions and allows for the differential assessment of intervention impacts—capabilities that fundamentally distinguish it from conventional cross-sectional designs. Comprehensive enumeration, coupled with proactive community engagement within distinct environments, alongside the application of validated digital data collection tools (REDCap), ensures the acquisition of high-quality, relevant longitudinal information. This dual-site structure is particularly valuable for identifying emerging health disparities, enabling the tailoring of evidence-based public health responses specific to each context and significantly enhancing the system’s contribution to multisite analytic collaborations and sustainable research capacity development in Zimbabwe.

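### The trend test named for change over time ignores repeated measurement of the same adults and gives no rural-minus-urban difference in change, which the article claims the design can compare robustly

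*Protocol article*

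**What the plan says.** - **Data Analysis** assigns the study of change to a single named test: "chi-square tests for trend will be used to analyze changes in NCD burden over time".
- The sentence after it reads: "Advanced statistical techniques, including regression and survival analyses, will facilitate robust estimation of NCD determinants and epidemiological transitions between the distinct study settings". No outcome, time term, site term or contrast is attached to it. Earlier in the section the article announces "comparative analyses designed to quantify rural versus urban differences", also without a form.
- **Follow-Up Procedures** has eligible adults interviewed and measured again at each round, with in-migrants added and out-migrants closed. Successive rounds therefore share most of their participants.
- **Study Aims** lists temporal trends in one aim. In another it sets out to "Quantify rural-urban differences in NCD burden, risk factor exposure profiles" and further outcomes. A difference in trend is not named as an aim.
- **Strengths and Limitations** claims that measuring both settings in the same way "facilitates robust comparisons of health transitions and allows for the differential assessment of intervention impacts".
- **Study Population and Sampling** gives power for two things: a "modest 2% absolute annual change in hypertension or diabetes prevalence (eg, from 30% to 32%) between surveillance rounds", and a rural-urban difference of 3% to 5%. Neither is a difference in change.
- **Results** places the end of baseline in December 2024 (rural) and March 2025 (urban), the first follow-up in the second quarter of 2027, and annual rounds after that through 2029.

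**The concern.** The method and the design do not match in two respects.

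**Independence.** The usual chi-square test for trend takes its variance from independent binomial samples. Here the same people, living in the same households, appear in successive rounds. The variance used is then not that of the estimated change.

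**The contrast.** The test can be run at each site, or once on pooled data. Run by site, it gives two separate results and no estimate of how they differ. Pooled, it averages over the contrast. Neither delivers a comparison of health transitions between settings.

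The article says findings will go to policymakers and will inform geographically targeted resource allocation. A statement that one setting is worsening faster would carry weight there. It should rest on an estimate of that difference and its uncertainty.

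**Working it through.** **1. The plan's own figures.** The precision calculation reproduces: 1.96² × 0.30 × 0.70 / 0.02² = 2017, and 2017 × 1.5 = 3025, stated as about 3000 per site. The figure of about 3500 per site per round for 30% versus 32% does not. The usual two-sided comparison of independent rounds at 80% power needs 8394. A formula for repeated measures reaches about 3525 only with a within-person correlation of about 0.58, which the article does not state. That is a separate issue. It matters here only because it shows how strongly the answer depends on whether rounds are treated as independent.

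**2. What the independence assumption does.** For two rounds with n adults seen in both, the variance of the change is

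[p1(1−p1) + p2(1−p2) − 2ρ√(p1(1−p1)p2(1−p2))] / n.

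Take p1 = 0.30, p2 = 0.32, n = 3500. The products p(1−p) are 0.2100 and 0.2176. The correlation ρ is an assumption, shown over a range.

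| ρ | SE of change (points) | Ratio to independence |
|---|---|---|
| 0 (as the test assumes) | 1.11 | 1.00 |
| 0.3 | 0.92 | 0.84 |
| 0.5 | 0.78 | 0.71 |
| 0.7 | 0.61 | 0.55 |

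On this account the trend test overstates the error and loses power. Household clustering can act the other way. The article's design effect of 1.5, given for the prevalence estimate, would multiply a standard error by √1.5 = 1.22. The net direction is not known from the article. Turnover of participants would move the ratios back towards 1.

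**3. What the contrast would look like.** With independent sites and the same inputs at each, the SE of the rural-minus-urban difference in change is √2 times the SE above. The 95% half-width is 1.96 times that: 3.06 points at ρ = 0, 2.56 at 0.3, 2.17 at 0.5 and 1.68 at 0.7, without clustering. The trend test provides none of these quantities.

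**4. If two site-level results were compared.** With equal true trends and independent sites, exactly one is significant with probability 2p(1−p), where p is the power per site. With independent rounds and 3500 per site per round:

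| Rounds, true rise at both sites | No design effect | Design effect 1.5 |
|---|---|---|
| Two rounds, 2 points (p = 0.440; 0.315) | 49.3% | 43.1% |
| Four rounds, 0.5 point per round | 42% | 34% |
| Four rounds, 0.75 point per round | 49% | 49% |
| Four rounds, 1.0 point per round | 30% | 46% |
| Four rounds, 2.0 points per round | about 0% | 1% |

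The four-round rows assume equal spacing. In a simulation of the two-round case (20,000 replicates, no design effect), a direct site-by-time test rejected in 4.9%, the nominal level.

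**5. Detectable difference in trend over four rounds.** Assume rounds at 0, 2.4, 3.4 and 4.4 years, an approximation to the dates in Results. The sum of squared time deviations is 10.67. The slope SE per site is √(0.21 × design effect / (n × 10.67)): 0.237 points per year for n = 3500 and design effect 1, and 0.314 for n = 3000 and 1.5. Multiplying by √2 × 2.80 gives 0.94 and 1.24 points per year. These values again treat rounds as independent.

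**The case against.** The strongest reply is that Data Analysis does not give the between-setting task to the trend test at all. The sentence that follows gives it to regression and survival analyses, and a regression across settings is where a site-by-time term would sit. This is a condensed article, and model terms are commonly left to the full protocol or analysis plan. That stands: the absence of an interaction term here does not show that the plan lacks one. It does not rescue the trend test, which is the method the article fixes for change over time and which does not fit repeated measurements on the same adults.

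Two stronger readings are tempting, and the documents support neither.

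- A reader might infer that a significant trend at one site and a nonsignificant one at the other will be reported as divergence, with a false-divergence rate of a third to a half. No section says the test is run by site or that p-values will be compared. The rate also depends on the slope, and is near zero at the article's own 2 points per year over four rounds.
- A reader might infer that the smallest detectable difference in trend is larger than the figures quoted for power. On the four-round calculation it is 0.94 to 1.24 points per year, below the quoted 2 points.

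It is also fair to say that a difference in trend is not a stated aim. The claim to compare transitions appears in the Discussion.

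**Conclusion.** The point holds in a limited form. The chi-square test for trend is a poor choice as the named analysis of change: its variance does not match a design that remeasures the same adults, and it cannot produce the comparison of transitions that the article claims. The later mention of regression leaves that contrast undefined.

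For a two-round change the true standard error would be 0.84 to 0.55 of the assumed one for correlations of 0.3 to 0.7. This assumes the same adults in both rounds and leaves out household clustering, so the net error could be smaller or reversed. No general false-divergence rate follows from the documents, and neither does a claim that power for divergence is worse than quoted. No follow-up round has yet taken place on the dates in Results, so the change can be made before any longitudinal data are seen.

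**What to change.** In Data Analysis, replace the trend test as the main analysis of change with one regression model for both sites:

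- **Terms:** site, calendar time, and site x time. Use actual dates rather than round number, because baseline ended at different times in the two sites and the gap to the first follow-up is longer than the later gaps.
- **Standard errors:** allow for repeated measures on individuals and for household clustering.
- **Reported quantity:** the rural-minus-urban difference in annual change, in percentage points per year, with its 95% CI. If a logistic model is used, obtain this from its predicted prevalences.
- **Interpretation:** base any statement that the settings diverge or converge on this estimate alone.

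If the full analysis plan already defines this contrast, one sentence saying so is enough. A detectable difference in trend should be added to Study Population and Sampling only after it has been computed for correlated rounds with a stated correlation; the 0.94 to 1.24 points per year above should not be used. The cost is slightly more analysis work. No additional data collection is needed.
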